## Test plan -Optimal@NRW-

V03, 15.02.2022

| Principal investigator    | Trial centre                                                  | CTC-A No. |
|---------------------------|---------------------------------------------------------------|-----------|
| [name] | Central Emergency Department, RWTH Aachen University Hospital | 19-019    |

Any decision regarding early trial termination for a trial participant or his/her exclusion will be discussed in advance with the clinical trial director. Dropout trial participants will be replaced.

The entire trial may be discontinued if one of the following criteria is met:

- The benefit-risk assessment on which the trial is based changes in such a way that the risks outweigh the benefits and/or the potential risks are no longer justifiable.
- Administrative problems that prevent the proper conduct of the trial.
- Serious protocol violations

## 9 Further treatment plan

No treatments will be given after the end of the trial. All trial participants return to their usual standard patient care after completion of the trial. This also applies to participants who have withdrawn their consent during the ongoing trial.

## 10 Statistics

### 10.1 Case number calculation and sample size

The average number of hospital days of persons in need of care is 13.16 days per quarter (Jacobs, Kuhlmeier & Greß, 2020). Taking into account the age structure >70 years (Federal Statistical Office, 2019), this results in an underlying average number of hospital days of 13.22 for the defined trial population. For the case number calculation, it is assumed that this can be reduced by 30% to 9.25 days. The assumption of the effect size was quantified by the specialists of the University Hospital Aachen. The internal dependence of the individual clusters is estimated with an intra-class correlation coefficient (ICC) of  $\rho=0.12$ , which is based on the ICC calculation of a preliminary trial by Hoffmann & Schmiemann (2017) for cluster-based studies in nursing home settings as well as the consideration of the trial design with several nursing homes in one cluster. With an  $\alpha$ -error of 0.05, a power of  $1-\beta = 0.90$  and an assumed standard deviation of 4.5, an underlying linear regression model results in a case number of 43 nursing home residents per nursing home and time interval. Due to the high mortality rate of the trial population (Vossius et al., 2018) and further factors of a possible dropout, a quarterly dropout of 12% is assumed, so that the number of cases increases to 49 nursing home residents per nursing home and time interval. This corresponds to a quarterly additional recruitment of approx. 6 nursing home residents per nursing home. This results in a total number of cases of **N=2,184 persons**. Expressed differently, this means a number of cases of  $n=1,173$  per cluster, which means that  $N=10,250$  observations are available for all persons across all clusters, which result from both longitudinal data of  $n=1,032$  persons and the  $n=1,152$  persons additionally recruited as cross-sectional data. Distributed over the individual phases of the trial design, this results in a

[figure not shown]

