| Number of cases and statistical considerations | 
The average number of hospital days of people in need of care is 13.16 days per quarter (Jacobs, Kuhlmeier & Greß, 2020). Considering the age structure >70 years (Federal Statistical Office, 2019), this results in an underlying average number of hospital days of 13.22 for the defined trial population. For the case number calculation, it is assumed that this can be reduced by 30% to 9.25 days. The assumption of the effect size was quantified by specialists of the University Hospital Aachen. The internal dependence of the individual clusters is estimated with an intra-class correlation coefficient (ICC) of <math>\rho=0.12</math>, which is based on the ICC calculation of a preliminary trial by Hoffmann & Schmiemann (2017) for cluster-based studies in nursing home settings as well as the consideration of the trial design with several nursing homes in one cluster. With an <math>\alpha</math>-error of 0.05, a power of <math>1-\beta = 0.90</math> and an assumed standard deviation of 4.5, an underlying linear regression model results in a case number of 43 nursing home residents per nursing home and time interval. Due to the high mortality rate of the trial population (Vossius et al., 2018) as well as other factors of a possible dropout, a quarterly dropout of 12% is assumed, so that the number of cases increases to 49 nursing home residents per nursing home and time interval. This corresponds to an additional quarterly recruiting of approx. 6 nursing home residents per nursing home. This results in a total case number of N=2,184 persons. In other words, this means a case number of <math>n=1,173</math> per interval, which means that <math>N=9,383</math> observations are available as cross-sectional data for all persons across all clusters, resulting both from longitudinal data of <math>n=1,032</math> persons and the <math>n=1,152</math> persons additionally recruited.
 |

[figure not shown]

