## Test plan -Optimal@NRW-

V03, 15.02.2022

| Principal investigator    | Trial centre                                                  | CTC-A No. |
|---------------------------|---------------------------------------------------------------|-----------|
| [name] | Central Emergency Department, RWTH Aachen University Hospital | 19-019    |

The disadvantages of this development are that the practitioner working in the hospital usually does not have the same knowledge of the medical history of the individual patient as the local doctor in private practice and, at the same time, the risk of confusion with resulting delirium increases for the patients due to the change of environment. Due to this development, among other things, the Expert Council on Health Care (Sachverständigenrat im Gesundheitswesen, SVR) recommended the necessity of a new regulation of intersectoral emergency care, including the outpatient and inpatient emergency service as well as the rescue service (Council of Experts 2018; German Medical Association 2018).

Optimal@NRW focuses on acute medical care of residents of care facilities. If a medical problem or a medical question currently arises in an inpatient care facility that exceeds the competences of the responsible nurse on site, the general practitioner is currently consulted by telephone and asked for advice. Outside the consultation hours of the GPs, the emergency medical service is available. This is often associated with long waiting times. If prompt care cannot be guaranteed, the ambulance service is usually called in to take the resident to an emergency room for further care, as on-site care is not possible in terms of time, personnel or logistics. The resident often remains in hospital afterwards. Out of 100 nursing home residents, about 20 persons are currently admitted to hospital once a year. Of these 20 retrospectively approx. 40 % are avoidable. They are referred to as ambulatory care sensitive hospitalizations (Jakobs et al. 2018; Sundmacher et al. 2015).

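### The sample size assumes 13.22 hospital days per resident per quarter with SD 4.5, which cannot be squared with the protocol's own admission rate, so the stated 90% power is unsupported

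*Protocol*

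**What the plan says.** Section 2.1 of the protocol defines the primary outcome as all days a participant spends in hospital within a period, same-day discharges included. Nothing restricts it to residents who are admitted.

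Section 10.1 bases the sample size on a published figure: "The average number of hospital days of persons in need of care is 13.16 days per quarter". After an age adjustment, the synopsis and section 10.1 both report that "this results in an underlying average number of hospital days of 13.22 for the defined trial population". For the effect, "it is assumed that this can be reduced by 30% to 9.25 days". With "an assumed standard deviation of 4.5", ICC 0.12, alpha 0.05 and power 0.90, "an underlying linear regression model results in a case number of 43 nursing home residents per nursing home and time interval". Then "a quarterly dropout of 12% is assumed", which raises 43 to 49 and leads to N = 2,184.

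Section 1 describes the same population differently: "Out of 100 nursing home residents, about 20 persons are currently admitted to hospital once a year".

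**The concern.** The planning mean is presented as an average over the trial population, and the outcome is zero for any resident not admitted in the quarter. If about one resident in five is admitted in a year, most resident-quarters are zeros. The mean should then be small and the SD large relative to it. Section 10.1 has the reverse: a mean of almost two weeks in hospital every quarter, and an SD about a third of that mean.

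The assumed difference of 3.97 days is 0.88 SD. If the real per-resident mean is well below 3.97, a reduction of that size cannot occur, and a 30% reduction is a far smaller standardised effect. A null primary result would then be read as evidence from a trial with 90% power when the trial had much less.

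**Working it through.** **Inputs**

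| Quantity | Value | Source |
|---|---|---|
| Control mean, SD | 13.22 and 4.5 days per quarter | Protocol 10.1, synopsis |
| Effect | 30%, to 9.25; difference 3.97 | Protocol 10.1 |
| Alpha, power, ICC | 0.05, 0.90, 0.12 | Protocol 10.1 |
| Admission rate | about 20 per 100 residents per year | Protocol 1 |
| Design | 24 homes, 4 clusters (so 6 homes each), 8 quarters, transition quarter excluded | Protocol 3.1, 4.1 |
| Residents living in the homes | more than 1,700, about 71 per home | Protocol 4.1 |

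**1. Reproducing the stated figure.** The protocol gives no formula. A two-sided comparison of two means gives 2 × (4.5 × (1.960 + 1.282) / 3.97)² = 27.0. A design effect of 1 + (6 − 1) × 0.12 = 1.60 gives 27.0 × 1.60 = 43.2, against 43 stated. The design effect is inferred from this match. Dropout: 43 / 0.88 = 48.9, i.e. 49. Total: 24 × 43 + 6 × 24 × 8 = 1,032 + 1,152 = 2,184. The stated numbers therefore follow from 13.22, 9.25 and 4.5.

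**2. Mean against admission rate.** 13.22 × 4 = 52.9 days per resident-year, and 13.22 / 91.25 = 14.5% of all days. At 0.20 admissions per resident-year this is 52.9 / 0.20 = 264 days per admission. Reading the 20 per 100 as a quarterly rate still needs 13.22 / 0.20 = 66 days per admitted resident. At 5% admitted per quarter (20 per 100 per year, spread evenly), with each staying the whole quarter, the mean is at most 0.05 × 91.25 = 4.6 days.

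**3. Mean and SD together.** If a share p of residents has any hospital day, SD ≥ mean × √((1 − p)/p), whatever the distribution. Solving for p with mean 13.22 and SD 4.5:

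p ≥ 1 / (1 + (4.5/13.22)²) = 0.896.

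About 90% of residents would need hospital days in every quarter. Conversely, a mean of 13.22 with p = 0.05 forces an SD of at least 57.6, and with p = 0.20 at least 26.4.

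**4. Consequence for power.** *Assumption:* 13.22 is days per hospitalised resident, with SD of stay s between 4.5 and 13.2. Then mean = p × 13.22 and variance = p × (s² + 13.22²) − mean². Power is from generalised least squares on home-period means, with 6 homes in each of 4 sequences, 8 periods, period effects, the transition cell dropped, two-sided 5%, 43 residents per home and interval, ICC 0.01 to 0.12 and cluster autocorrelation 0.8 to 1.

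| Hospitalised per quarter | Mean | SD | 30% reduction | Effect in SD | Power |
|---|---|---|---|---|---|
| 5% (section 1's rate) | 0.66 | 3.1–4.1 | 0.20 | 0.05–0.07 | about 9–20% |
| 10% | 1.32 | 4.2–5.8 | 0.40 | 0.07–0.09 | about 12–37% |
| 20% (four times that rate) | 2.64 | 5.7–7.9 | 0.79 | 0.10–0.14 | about 22–67% |

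With 49 residents the maximum is 22% in the first row and 73% in the last. An illustrative within-resident correlation of 0.2, allowing for the open cohort, raises the upper ends at 43 residents to 24%, 44% and 77%. At ICC 0.12, cluster autocorrelation 1 and s = 4.5, 90% power would need about 365, 174 and 79 residents per home and interval respectively. The plan has 43, and about 71 live in each home.

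**The case against.** Five points deserve an answer.

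- *The mean alone is not impossible.* This stands in part: over a year, extremely long stays could produce it. The SD of 4.5 closes that route, because the bound in step 3 is mathematical and needs no outside source.
- *Section 1's rate is one approximate background sentence and could itself be the loose figure.* That is fair. The documents show a conflict but do not prove which figure is right. Even so, reading the rate as 20% per quarter comes nowhere near 90%. Same-day visits count too, but at about one day each they cannot close the gap.
- *Reading 13.22 as days per hospitalised person is a guess.* It is, because the protocol does not say so and the source is not available. It is used only to size the consequence, and the incompatibility does not depend on it.
- *The power figures are conditional.* This also stands. The ICC may not carry over to the per-resident scale, and within-resident correlation raises power somewhat. They are illustrations, not the trial's actual power.
- *With its own inputs the stepped-wedge design has essentially 100% power, so there is slack.* That surplus comes from the 0.88 SD effect and disappears once the inputs match section 1.

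Bias and type I error are unaffected, and a confidence interval would partly expose the imprecision. The harm lies in the power claim.

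**Conclusion.** The concern holds. No arithmetic slip was found in getting from the inputs to 43; the inputs themselves are wrong for the outcome. A mean of 13.22 with SD 4.5 would need about 90% of residents to have hospital days every quarter, against about 20 per 100 admitted in a year according to section 1. No other part of the protocol supplies a per-resident mean or SD that resolves this.

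The assumed reduction of 3.97 days is six times the 0.66-day mean implied by section 1's rate if 13.22 is the mean for hospitalised residents only (3.97 / 0.66 = 6.0). Under that assumption power is about 9% to 24% at section 1's rate and stays below 90% even at four times that rate. The inconsistency is certain from the document; the exact power is not, and depends on the true share hospitalised, the spread of stays and the correlations.

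**What to change.** In section 10.1 and the synopsis, give the mean and SD of hospital days per resident-quarter with zeros included, and the effect on that scale. Two sources are already foreseen in section 6: the health-insurance routine data from 2019, which cover only insured persons of the participating funds, and control-phase data used in a pooled or non-comparative way. Then recompute power, or the detectable difference, for the fixed 24 homes and 8 quarters, using a stepped-wedge model suited to a skewed outcome with many zeros. State the formula and the correlation assumptions. Reconcile the admission rate in section 1 with the new inputs.

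Version 03 is dated 15.02.2022, after the first cluster's intervention start on 1 February 2022 (section 3.2). The new figures should therefore be labelled a mid-trial restatement and shown beside the planning calculation.

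The cost is a recalculation and revised wording. The stated power will be less favourable. No additional participants and no change to enrolment are needed.

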The trial design is a cluster-randomised trial at the level of the nursing homes (inpatient sector) in the form of a stepped-wedge design. A consideration at the nursing home level supports the feasibility of the project, since a randomised allocation at the patient level would require the simultaneous implementation of the new form of care and the standard care within a facility (Brown & Lilford, 2006). This is not usefully realizable, because the internal validity of the trial results would be threatened by the Hawthorne effect (Gelman & Hill, 2006). In the stepped wedge design, observation of all clusters begins simultaneously, with all clusters initially in the control phase. Subsequently, the clusters move into the intervention phase at equal intervals, randomised in terms of timing. Thus, from an ethical perspective, the design offers the advantage that every participant receives the intervention until the end of the trial, as a positive added value of the project is assumed, while at the same time preserving randomised evidence through a randomised start of the intervention (Hemming, Haines, Chilton, Girling & Lilford, 2015). The stepwise establishment can also overcome logistical and practical implementation difficulties that arise in trial designs with simultaneous intervention start. Through a transition phase between the control and intervention phase, training measures for the nursing staff as well as technical installations can be carried out. The data collected during the transition phase are not included in the evaluation.

In the actual project, four clusters with a homogeneous number of nursing homes per cluster are formed, in order to ensure intra-cluster validity. In the sense of an 'Open Cohort', both longitudinal data (constant trial population over the entire course of the trial) and cross-sectional data (different patients in the individual stages) are included, in order to include the average mortality rates (Vossius, Selbæk, Šaltytė Benth & Bergh, 2018) of nursing home residents. The respective stages cover an interval of three months in terms of one quarter per year. In order to obtain a meaningful control and intervention group, the minimum number of surveys in both phases is two stages (six months).

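### The stated 90% power is not the power of 43 residents per nursing home and quarter, and the protocol does not say to which unit the 43 belongs

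*Protocol*

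**What the plan says.** Section 10.1 gives an "underlying average number of hospital days of 13.22 for the defined trial population" and says "it is assumed that this can be reduced by 30% to 9.25 days". It adds "an assumed standard deviation of 4.5", an ICC of 0.12, an alpha of 0.05 and a power of 0.90. From these, "an underlying linear regression model results in a case number of 43 nursing home residents per nursing home and time interval". The synopsis, in its row on case numbers, says the same: "results in a case number of 43 nursing home residents per nursing home and time interval".

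The ICC is attributed partly to an earlier nursing-home study and partly to "the consideration of the trial design with several nursing homes in one cluster". In Section 3.1, "four clusters with a homogeneous number of nursing homes per cluster are formed", followed over eight quarterly stages. Each cluster has at least two control and two intervention stages, and the transition stage is left out of the analysis. Section 4.1 gives 24 homes, so six per cluster.

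The per-home unit is carried through the rest of the calculation: 43 x 24 = 1,032 persons; 43/0.88 = 48.9, rounded to 49, for 12% dropout; about 6 replacements per home and quarter, 6 x 24 x 8 = 1,152; and 1,032 + 1,152 = 2,184.

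**The concern.** A requirement of 43 residents in each of 24 homes in each quarter is very large for a difference of 3.97 days against an SD of 4.5, which is 0.88 SD. Even with an ICC of 0.12, a stepped wedge of that size should have power far above 90%. Either the 43 belongs to a different unit, or the 0.90 is not the power of the size stated.

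The 1,032, the 49, the 1,152 and the N of 2,184 are all built on the 43. If power and size do not belong together, a reader cannot tell from the protocol what effect the trial can detect, or what a null result would exclude.

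**Working it through.** **Inputs from the protocol.** Difference 13.22 - 9.25 = 3.97; SD 4.5 (variance 20.25); ICC 0.12; alpha 0.05; 4 clusters of 6 homes; 8 quarters; transition quarter excluded. Cluster 1 has control quarters 1-2, transition 3, intervention 4-8. Cluster 4 has control 1-5, transition 6, intervention 7-8.

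**Assumptions, because the protocol does not state them.** Two-sided test; fixed quarter effects; a random effect per unit; a resident's repeated quarters treated as independent given the unit; cluster autocorrelation r, with r = 1 meaning constant correlation across quarters.

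**Formula.** For m residents per unit and quarter, the covariance matrix V of a unit's quarterly means has between-unit variance 0.12 x 20.25 = 2.43. Its diagonal is 2.43 + 17.82/m and its off-diagonal is 2.43r. SE is the square root of the treatment element of (sum of X'V⁻¹X)⁻¹. Power is Φ(3.97/SE - 1.96), or its t version with df = units - 2.

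**Recovering 43, route A: four units, r = 1, central t on 2 df (critical value 4.303).**
- m = 43: SE 0.641; 3.97/0.641 - 4.303 = 1.89; power 0.9003.
- m = 42: power 0.895, so 43 is the smallest m that reaches 0.90.

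This 43 is per cluster and quarter, about 7 per home. The match is fragile. A noncentral t gives 0.853 at 43 and needs 52. A normal approximation needs 12. The unrounded difference of 3.966 gives 0.8998 at 43 and needs 44.

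**Recovering 43, route B: two groups with a design effect.** n = 2 x (1.96 + 1.2816)² x 4.5² / 3.97² = 27.0 per group, and 27 x [1 + (6 - 1) x 0.12] = 43.2. This uses no stepped-wedge structure. Rounding 27.0 up to 28 first would give 28 x 1.6 = 44.8 instead.

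**Power at the size actually stated, 43 per home and quarter.**

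| Units | m per unit and quarter | SE (r = 1) | Power |
|---|---|---|---|
| 24 homes | 2 | 1.152 | 0.93 (0.91 with t, 22 df) |
| 24 homes | 43 | 0.262 | above 0.999 |
| 4 clusters | 6 x 43 = 258 | 0.263 | 0.996 (t, 2 df) |

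**Sensitivity to r, 24 homes, 43 per home.** Power stays above 0.999 throughout. The difference detectable with 90% power, (1.96 + 1.2816) x SE, is:

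| r | Detectable difference (days) |
|---|---|
| 1 | 0.85 |
| 0.8 | 1.24 |
| 0.5 | 1.64 |
| 0 | 1.93 |

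**Sensitivity to r, four clusters of 258, normal approximation.** Power is 0.9997 at r = 0.8, 0.948 at 0.5, 0.912 at 0.4, 0.844 at 0.2 and 0.826 at 0. A t on 2 df is harsher: at r = 0.8, SE is 0.740, 3.97/0.740 - 4.303 = 1.06, and power is about 0.80.

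**The case against.** The strongest reply is that 43 does follow from the stated inputs. Route A uses the protocol's four clusters, eight stages and excluded transition stage, and 43 is the smallest cell that reaches 0.90. The ICC wording also points to the cluster of several homes as the unit. This stands far enough to rule out three stronger readings.

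- A reader might infer that no stepped-wedge structure entered the figure. Route A shows that it may have.
- A reader might infer that the sponsor took six homes as the cluster size in a two-group formula. Route B lands on 43 only with favourable rounding, and the protocol states no such formula. Two unrelated routes reach the same number, so the number identifies neither.
- A reader might infer from the 2 residents per home in the table that the trial is about twenty times too large and could be cut. That needs an ICC of 0.12 at home level, 24 independent homes and an SD of 4.5. The first two are not stated, and the third is an assumption of the plan. At 43 per home, power for 3.97 days falls to 90% at an SD of 21.1 if r = 1, or 9.2 if r = 0.

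The reply does not rescue the text as written. Under route A the 43 is per cluster and quarter, whereas the protocol attaches it to each home and multiplies by 24.

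It is also fair to say that on the stated inputs the mismatch lies towards too much power with 24 homes as units. The point is therefore about a wrong power statement, not an underpowered trial.

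**Conclusion.** The point holds in this form: the stated power of 0.90 does not belong to the stated size of 43 residents per nursing home and quarter. On the protocol's inputs, power at that size exceeds 0.999 with 24 homes as units at every cluster autocorrelation tried from 1 to 0. It is 0.996 with four clusters of 258, constant correlation and t on 2 df.

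With four units and lower autocorrelation, power can fall to 0.90 or below. The protocol gives neither the unit nor the correlation that would produce this, so that reading does not support the stated figure either. Which route produced the 43 cannot be told from the document.

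These results take the 3.97-day difference, the SD of 4.5 and the ICC of 0.12 as given, and add a two-sided test and fixed quarter effects. They do not show a shortfall for the 24-home unit, and they are no reason to reduce recruitment.

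**What to change.** Keep the recruitment target. In Section 10.1 and the matching synopsis row:

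1. State whether the 43 and the ICC of 0.12 apply to a nursing home or to a cluster of six homes.
2. State the number of units in the calculation, the sidedness, the test and its degrees of freedom, and the assumed correlation between quarters.
3. Recompute power or the detectable difference with a stepped-wedge mixed model for 24 homes at 43 to 49 residents per home and quarter, with quarter effects and the transition quarter excluded.
4. Report the result over a range of between-quarter correlation. On the present inputs, the detectable difference at 43 per home runs from 0.85 days (r = 1) to 1.93 days (r = 0).
5. Replace the statement of 90% power with that result, and describe 2,184 as the recruitment target whose power has been assessed in this way.

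The cost is one recalculation and an amendment of the wording. No extra participants and no change of design are needed.
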